### **D.3.2. Treatment Integrity**

Standardized procedures will be followed to insure the prevention sessions' integrity. The intervention manual includes a detailed format to be used for each session. Each team will be provided with materials designed to facilitate correct execution of the session protocol, including an outline of each session, a checklist of the materials necessary for each activity, the specific theme of each task, and forms for in-session notes.

Presentation of targeted processes on videotapes also will help to ensure the intervention's integrity. The field supervisor also will make unannounced direct observations of the sessions. To assess program fidelity, all sessions will be videotaped and scored for curriculum coverage and protocol adherence using instruments developed for SAAF. Two judges will score one of every four sessions to assess interrater reliability (kappas).

### **D.3.3. Logistics**

A meeting site will be established in each county at a community facility in a central location that is easily accessible to program participants. Churches and schools provide ample space for classrooms, waiting areas, and parking.

### **D.3.4. Engagement Procedures**

Several strategies from SAAF will be used in the proposed program to address scheduling conflicts, transportation needs, and child care requirements. During the pretest, family members will be asked about their weekly schedules and sessions will be planned to accommodate the schedules of as many families as

possible. During the first half hour of each meeting, dinner will be served to family members attending the session. Leaders will arrange transportation for any families who need it and care will be provided for any children who come with the families. An intensive reminder protocol also will be used throughout the program. Community liaisons will call all participants before the program begins and prior to each weekly session to encourage their involvement. Reminder postcards will be sent from the CFR each week, highlighting the focus of the upcoming meeting. A community liaison will call participants who miss a meeting to remind them of the next meeting and address any barriers to attendance. In SAAF, these strategies resulted in attendance rates that were higher than those of middle-class European Americans participating in a family-centered substance use prevention program (Spath et al., 2001).

#### **D.4. SAAF–HS Program Structure and Content**

The proposed intervention will be structured according to the SAAF delivery system. The prevention program will consist of seven consecutive weekly meetings, with separate caregiver and adolescent skill-building curricula and a family curriculum. Each meeting will include separate, concurrent sessions for caregivers and adolescents, followed by joint sessions during which the adolescents and their caregivers review, discuss, and practice the skills they learned in their separate sessions. Videotapes portraying family interactions and intrapersonal processes will be used in all sessions to ensure consistent presentation of key points. Each session will include a homework review, didactic presentation, group discussion, and skill-building activities that reinforce learning. The concurrent and family sessions will each last 1 hour; thus, adolescents and caregivers will receive 14 hours of prevention training. This dosage corresponds to Tobler's (2000) recommendations, based on a meta-analysis, for dosage levels needed to promote changes in intervention participants' behavior.

The complete SAAF–HS curriculum is presented in Appendix A. The program content is based on the causative model presented in Section B.5. The caregivers' curriculum focuses on enhancing developmentally appropriate, competence-promoting parenting strategies; promoting adolescents' racial identity and providing youth with strategies for dealing with discrimination; supporting academic engagement; providing information about HIV/AIDS and other sexually transmitted diseases; and communicating expectations about high-risk behavior. The adolescents' curriculum will address developing future orientations and formulating plans for continuing education and employment; enhancing academic engagement; developing problem-focused coping and adaptive strategies for dealing with discrimination; enhancing youths' ability to implement protective behaviors should they decide to engage in sexual activity; and understanding the effects of substance use in undermining protective sexual behavior.

#### **D.5. Attention-control Condition Structure and Content**

Participants randomly assigned to the attention-control condition will participate in a 7-week family-centered program designed to promote healthful behaviors among adolescents by encouraging good nutrition, exercise, and informed consumer behavior. The structure of the attention-control program will be identical to that of the SAAF–HS program: Each weekly meeting will include separate, concurrent 1-hour caregiver and youth sessions followed by a 1-hour family session, providing 14 hours of training. The content of the attention-control condition will be taken from the FUEL™ program, which includes four units for parents and youth. The first unit, Skin Deep, addresses media literacy, self-esteem, and body image, with an emphasis on consumer education. Energy for Action, the second unit, focuses on strategies for establishing a healthful diet. The third unit, The Perfect Machine, explains the benefits of physical activity and suggests strategies for incorporating it into the youths' daily lives. Taking on the World, the fourth unit, deals with positive activism for promoting healthful lifestyles in the youths' communities. Like SAAF–HS, FUEL™ includes videotaped exemplars of targeted behaviors and processes. During project year 1, [name], the CFR curriculum developer, will adapt the FUEL™ structure to make it identical to that of SAAF–HS. The procedures for training facilitators, ensuring intervention integrity, and engaging participants will also be equivalent to those used in the SAAF–HS implementation.

#### **D.6. Data Collection**

One 2-hour home visit will be made to each family for data collection at the pretest, posttest, and long-term follow-up assessments. To minimize cultural bias, African American students and community members, many of whom have worked at the CFR for many years, will serve as assessment assistants.

##### **D.6.1. Intervention Assessment**

Computer-assisted self-administered interviews using audio enhancements (ACASI) will be used to collect data from youth and caregivers. The interview measures will be administered via ACASI with the guidance of Assessment Assistants. The assistants, who will be blind to families' assignment to the SAAF–HS or attention-control condition, will arrange home visits with participants. The assistants will set up a computer for each family member at places in the residence that the family designates as private, then enter the participants' ID numbers and the commands necessary to begin the appropriate instruments. After leading the participants through a series of warm-up exercises and verifying that they are comfortable using the computers, the Assessment Assistants will remain available to help participants upon request. When data are returned to the CFR, the project coordinator will immediately check their completeness and integrity and ensure the ID numbers' accuracy. Within 8 business hours of data collection, a computer specialist will upload the data to a secure server; all data are backed up to a storage area network on an hourly basis.

**D.6.1a. Training of Assessment Assistants.** Assessment Assistants will be selected based on their previous experience with collecting data and interviewing adolescents about sensitive topics. Prior to administering the baseline assessment, they will receive 20 hours of intensive training and supervised practice that will address building rapport, using the ACASI system, and helping participants to use the system. Assistants also will meet each week with the Project Director to discuss any problems that arise. Prior to the follow-up assessments, training updates will be conducted in which any changes to the interview items or assessment procedures will be reviewed.

#### **D.6.2. Process Evaluation of the Prevention Program**

Using session attendance and program fidelity data (see section D.3.2), a dosage score will be calculated for each study participant. Both parents in two-parent families will be encouraged to attend each session of the program; in single-parent families, the parent and an extended family member who assists with the youth's upbringing will be encouraged to attend. If two adults cannot come, attendance of one will be encouraged as preferable to attendance of neither.

#### **D.7. Measures**

We will use multi-informant, multiple indicator strategies to assess the constructs underlying the intervention theory. Potential time-varying factors and risk factors that could compromise SAAF–HS effects will also be measured: parental depression, parental substance use, changes in parental relationships or employment situations, and personal life stressors. Including these variables in the longitudinal assessment will enable the investigators to determine whether the risk factors compromise the prevention program's efficacy or, conversely, the prevention program reduces the risk factors' impact. The measures can be found in Appendix E.

##### **D.7.1. Demographics**

The demographic interview was designed and tested in Georgia with samples of single mothers and married parents. Primary caregivers will report their yearly income, per capita income, employment status, duration of unemployment during the past 2 years, hours worked per week, education level, numbers of children and adults in the household, and relations of all household members to one another.

##### **D.7.2. Competence-Promoting Parenting and Responsive Family Relationships**

Five indicators comprise the parenting construct: involved-vigilant parenting; supportive, affectively positive family relationships; communication and expectations about risk behavior; parental involvement in adolescents' academic pursuits; and adaptive racial socialization.

**D.7.2a. Involved-vigilant parenting.** Adolescents and caregivers will report involved-vigilant parenting using an instrument from [name] and [name]'s longitudinal, developmental research with rural African American families ([name], Ge, et al., 2001; 2003). The scale's 19 items assess parental involvement, inductive discipline, consistent discipline, and monitoring. Responses to the items are summed. Cronbach's alphas exceed .70 ([name], [name], Gerrard, et al., 2004).

**D.7.2b. Supportive, affectively positive family relationships.** Adolescents and caregivers will assess support in their family relationships with the Family Support Inventory (Wills et al., 2003), a 14-item measure of perceived availability of emotional and instrumental support. Internal consistency ranged from .82 to .88 for emotional support and .76 to .83 for instrumental support for rural African Americans caregivers and adolescents. The scales consistently predict low substance use, high self-regulation, and resilient coping (Wills et al., 2000, 2003). Four items that Carver, Scheier, and Weintraub (1989) developed will be used to assess the frequency with which family members provide emotional support. Cronbach's alphas in [name] and [name]'s prior

prevention research ranged from .78 to .87 ([name], [name], Gerrard, et al., 2004). The Interaction Behavior Questionnaire (Prinz et al., 1979) assesses affective involvement and positivity in family communication. Cronbach's alphas for this scale with one of [name] and [name]'s longitudinal research samples were .85 for caregivers and .79 for youths ([name], [name] et al., 2002). The Discussion Quality Scale ([name] & Flor, 1998) will be used to assess parent-adolescent discussions regarding school, peers, alcohol, other drugs, and sex. For each topic, caregivers and adolescents are asked about the frequency of conversations, the relative contributions of parent and child to the conversations, and the frequency with which discussions become arguments. In [name] and [name]'s prior research, Cronbach's alphas were .84 for caregivers and .79 for adolescents.

**D.7.2c. Communication and expectations about risk behavior.** Adolescents and caregivers will complete a 6-item scale that assesses parents' communication of expectations about substance use and sexual behavior (Spath, Redmond, & Shin, 1998). Three items, which concern clear parental expectations about the behavior in question and association with peers who engage in it, are rated twice, once regarding substance use and once regarding sexual behavior. Parents' communication about sexual risk behavior also will be assessed with a 5-item scale that DiClemente and colleagues developed for use with African Americans. Adolescents and parents report the frequency with which they communicated about pregnancy prevention, STD prevention, HIV prevention, and condoms during the past 6 months. This measure was internally consistent ( $\alpha = .88$ ) and associated with condom self-efficacy. The Process of Sexual Communication Scale ([name], [name], Gerrard, et al., 2004), used with youth in SAAF, assesses the quality of parent-child conversations regarding sex from caregivers' and adolescents' perspectives. Reliabilities exceeded .70 for both parent and youth reports.

**D.7.2d. Parental involvement in youths' academic pursuits.** Parental involvement in youths' schooling will be assessed from caregivers' and adolescents' perspectives using parallel versions of a 15-item scale that [name] et al. (1995) developed to assess parent participation in school-related activities. Cronbach's alpha for this scale exceeded .80. Adolescents and caregivers also will complete parallel versions of a 9-item scale adapted from the National Educational Longitudinal Study of 1988 (Ingels et al., 1994). The measure assesses parents' supervision of homework and discussions of academic planning. Internal consistency for this scale with 9th-grade students was .79

**D.7.2e. Adaptive racial socialization.** Adolescents and caregivers will complete Stevenson's (1997) Scale of Racial Socialization for Adolescents (SORS-A). The measure includes 4 subscales that assess various aspects of adaptive racial socialization. Cultural Pride Reinforcement indexes encouragement to take pride in African American culture; Racism Awareness Teaching involves helping adolescents to be alert to racism and its consequences; Life Achievement Struggling emphasizes overcoming obstacles to achievement; and Extended Family Caring measures relatives' caregiving support

### **D.7.3. Adolescent Stressors**

**D.7.3a. Racism.** Adolescents, friends, and caregivers will report their experiences with racism using the Schedule of Racist Events (SRE; Landrine & Klonoff, 1996). We will use the SRE's Frequency of Unfair Treatment Based on Race and Stress of Racial Unfairness subscales. Respondents rate the occurrence and stressfulness of racially based unfair treatment by school officials, business employees, legal officials, neighbors, church members, friends, and strangers. In developmental research, Cronbach's alphas for youth and caregivers exceeded .75 for both subscales ([name], Chen, et al., in press).

**D.7.3b. Educational and occupational opportunities.** The Total Resources subscale ( $\alpha = .95$ ) from the Community Problems and Resources Scale (Forehand & [name], 2000) will be used to assess the availability of 19 competence-promoting community characteristics such as job training, educational facilities, social organizations, and transportation. For the proposed study, additional items were developed to target educational and job opportunities.

### **D.7.4. Risk Factors and Time-Varying Life Circumstances with Potential Influence on SAAF-HS Efficacy**

**D.7.4a. Financial stress.** Caregivers will report chronic financial difficulties using scales developed for [name] and [name]'s longitudinal research ([name], Ge, et al., 2001, 2003): Unmet Material Needs, Can't Make Ends Meet, Financial Adjustments, and Negative Financial Events. These scales' reliabilities with rural African American samples range from .69 to .80.

**D.7.4b. Caregivers' life stress.** Caregivers will report the stressors they encountered during the previous year, such as divorce or separation, violent victimization of a family member, and incarceration of a family

member (Kim, [name], et al., 2005).

**D.7.4c. Caregiver depression.** The Center for Epidemiologic Studies Depression Scale (Radloff, 1977), which was designed for administration to community samples, will be used to assess caregiver depression. Internal consistency with rural Georgia samples averages .84 ([name], [name], et al., 2002).

**D.7.4d. Caregiver substance use.** Caregivers will report their own substance use on the Parent Alcohol/ Drug Use History (Collins, Parks, & Marlatt, 1985). Items assess drinking in a typical week and both lifetime and recent use of marijuana, stimulants, sedatives, psychedelic drugs, cocaine, heroin, and opiates. Internal consistencies for caregivers in [name] and [name]'s prevention research ranged from .79 to .81.

**D.7.4e. Caregiver employment and relationship status.** Caregivers' reports of changes in employment, marital status, or cohabitation will be included in each year's demographic interview.

#### **D.7.5. Negative Emotions**

Adolescents and caregivers will report their negative emotions using the Depression, General Anxiety, and Hostility subscales of the Brief Symptom Inventory (Derogatis & Melisaratos, 1983), a measure of generalized distress (Piersma, Boes, & Reaume, 1994) that detects low-level negative emotions in community samples. [name] and Ge (2001) reported Cronbach's alphas exceeding .75 for rural African American youth and adults.

#### **D.7.6. Adolescent Protective Mediators**

**D.7.6a. Future orientation.** Adolescents will report their time orientations using a version of Zimbardo's Time Perspective Inventory (Zimbardo & Boyd, 1999) that Wills and colleagues adapted for use with multiethnic samples of adolescents (Wills, Sandy, & Yaeger, 2001). The Future subscale assesses the formulation of goals and plans to achieve them ( $\alpha = .77$ ); the Present subscale indexes an orientation toward present enjoyment, pleasure, and excitement ( $\alpha = .79$ ). Time perspective is associated with self-regulation, anger-based coping, and self-esteem (Wills et al., 2001). Adolescents and their friends also will use a scale developed for SAAF to report their ability to set, sustain, and achieve future-oriented goals. Cronbach's alpha at SAAF pretest was .72, and the scale was sensitive to program effects ([name], [name], Gerrard, et al., 2004).

**D.7.6b. Self-regulation.** Adolescents will complete the Self-Control Inventory (Wills & Stoolmiller, 2002), which includes 25 items distributed among seven subscales (Soothability, Dependability, Planning, Problem Solving, Impatience, Distractibility, and Angerability). Wills and associates (Wills et al., 2000, 2003) reported reliabilities of .73 to .83 with rural African American adolescent samples. Caregivers will complete the Self-control and Lack of Self-control subscales of the Self-Control Scale (Humphrey, 1982), which [name] and [name] have used extensively with African American children and adolescents ([name], [name] et al., 2002; [name] et al., 2004). The subscales assess goal setting, formulation of plans to attain goals, and persistence or lack thereof. Cronbach's alphas consistently exceed .75.

**D.7.6c. Emotion regulation.** Adolescents will report their coping styles using Wills and Hirky's (1996) Coping Processes Inventory. Respondents are presented with definitions of various coping behaviors and asked how often they use each approach for dealing with problems concerning school, parents, health, and sadness. Internal consistencies in a multiethnic sample of adolescents (Wills et al., 2002) exceeded .78. The proposed project will include the measure's anger-based, helpless, substance use, and avoidant coping subscales.

**D.7.6d. Racial identity.** Adolescents will report their racial identity using the Centrality and Regard subscales of the Multidimensional Model of Racial Identity for African Americans (Sellers et al., 1997). The investigators used these scales with African American youth in previous prevention research ([name] et al., 2005). Centrality ( $\alpha = .70$ ) indicates the importance of respondents' race to their self-definitions and Regard ( $\alpha = .73$ ) refers to affective and evaluative perceptions of one's race.

**D.7.6e. Academic engagement.** Adolescents will report their academic engagement using a 20-item scale that [name] developed for use with rural African American youth; Cronbach's alpha = .90 ([name], Ge et al., 2003).

**D.7.6f. Negative attitudes about substance use and high-risk sexual behavior.** Adolescents will report their own attitudes about substance use and high-risk sexual behavior using a scale that [name] and colleagues ([name], [name], Gerrard, et al., 2004) developed for rural African American youth. Reliabilities exceeded .80.

**D.7.6h. Resistance efficacy.** Adolescents will report their substance use resistance efficacy with the Drinking Refusal Self-Efficacy Questionnaire (DRSEQ; Young, Oei, & Crook, 1991). The DRSEQ has demonstrated internal consistency and construct validity and is associated with substance use quantity (Lee & Oei, 1993; Young & Oei, 2000).

**D.7.6g. HIV prevention knowledge.** Adolescents will report their HIV knowledge using a scale that DiClemente and Wingood developed in their ongoing research with African American adolescents (DiClemente et al., 2004). The 23-item scale uses a True-False-Don't Know response set. Correct responses are summed to create a composite score. Internal consistency is .86.

**D.7.6h. Expectancies and attitudes about sexually self-protective behavior.** Adolescents will report their expectations about condom use on a version of the Condom Attitude Scale (St. Lawrence, Reitman, Jefferson, & Alleyne, 1994) adapted for administration to teens with low literacy. The internal consistency of the scale with African American adolescents participating in the SiHLE trial was .83. Outcome expectancies for communicating with a sexual partner about HIV-risk-related behavior will be assessed with the Sexual Communication Attitude Scale, a measure that DiClemente and Wingood developed to assess communication between adolescent sexual partners. This revised scale will be pilot tested and its psychometrics properties established prior to its use in the proposed research program.

**D.7.6i. Self-efficacy for sexually protective behavior.** Adolescents will report their self-efficacy for condom use on an 11-item scale that Wingood and DiClemente developed to measure African American adolescents' beliefs about their ability to use condoms effectively. The scale has an internal consistency of .84 (DiClemente et al., 2004). Adolescents and their friends also will report their confidence in communicating with partners about protective sexual behavior using a 7-item scale that Wingood and DiClemente developed. The scale demonstrated satisfactory internal consistency in the SiHLE study ( $\alpha = .82$ ).

#### **D.7.7. Adolescents' Outcomes**

**D.7.7a. Substance use.** The substance use assessment is designed to address its multidimensional nature (Newcomb, 1992). From three well-validated measures, items were selected for their sensitivity to intervention effects at several levels of substance use. At the initiation level, group differences in the proportion of participants who transition from nonuse to use during the study can be detected. At the escalation level, group differences in the proportion of participants who increase their frequency/intensity of use during the study can be assessed. At the problem use level, group differences in specific substance-related behaviors and problems can be determined. The basic items in the measure are those included in the Monitoring the Future study (Johnston et al., 2004) that assess lifetime, annual, and 30-day prevalence and frequency of cigarette smoking, alcohol use, binge drinking, and marijuana use. For the purposes of the proposed study, a 6-month assessment at the long-term follow-up will be added. A checklist of other drugs includes lifetime use of LSD/acid, MDMA/Ecstasy, cocaine, heroin, other opiates, amphetamines, non-prescribed tranquilizers, and inhalants. Problems associated with substance use will be indexed using items from the Minnesota Student Survey for high school students (Harrison, Fulkerson, & Beebe, 1998) These scales include items assessing dependence (e.g., had to use more to get same effect, tried to cut down but couldn't) and negative consequences of use (e.g., use hurt relationships with friends or family, use interfered with other activities, use resulted in problems with law, missed school or work because of use).

**D.7.7b. High-risk sexual behavior.** The primary outcome for this variable is the proportion of vaginal and anal sexual acts in which condoms were used during the 30 days prior to the ACASI assessment. This measure is derived by dividing the number of protected encounters by the total number of encounters. This ratio is one of the most commonly used measures of outcome efficacy in HIV prevention trials (Celentano et al., 2002; Chesney et al., 2003; Gordon, Forsyth, Stall, & Cheever, 2005; Hobfoll et al., 2002; Rosser et al., 2002). Other self-reported sexual behaviors to be assessed include the number of unprotected vaginal and anal sexual encounters during the previous 3 months and condom use during the most recent instance of sexual intercourse. Information on number and types (primary, casual, new) of sexual partners; frequency of oral, anal, and vaginal sex; use of alcohol and other drugs prior to sexual intercourse; STD infection; pregnancy; and partners' risk status (e.g., sexual partner has other partners) will also be gathered.

Researchers widely recognize that participants' reports of their sexual practices might be inaccurate, either unintentionally or intentionally. We will take several steps to increase the self-report measures' validity. To minimize inaccurate recall, only sexual behavior that occurred during a relatively brief time period (i.e. during the past 30 days, during the past 3 months, and at last sexual intercourse) will be addressed. Participants also will be given a calendar on which the relevant dates are clearly marked. ACASI methodology also has been demonstrated to increase respondents' willingness to provide frank responses to sensitive questions about their sexual behavior (Macalino et al., 2002).

**D.7.7c. Deviant behavior.** Theoretically, antisocial behavior is related to substance use and high-risk sexual activity (Jessor, 1991), perhaps through a common cause such as parents' ineffective monitoring and discipline (Leigh & Stall, 1993). Adolescents will use a checklist from the National Youth Survey (Elliott, Ageton, & Huizinga, 1985) to report their own deviant behavior during the past 3 months and the proportion of their friends who engaged in the same behavior during that time period.

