### **D.8.2. Analyses for Aims 1 and 2: Primary Outcomes**

The primary issue to be addressed in Aims 1 and 2 is SAAF-HS's effectiveness in deterring the onset and escalation of substance use and high-risk sexual behavior across the 18 months separating the pretest and long-term follow-up assessments. A dramatic growth in substance use and high-risk sexual behavior is likely to occur across measurement points, which include the beginning of 10th grade, middle of 10th grade, and beginning of 11th grade. SAAF-HS's impact on each of the outcomes will be examined in three ways: on posttest (middle of 10th grade), on long-term follow-up (beginning of 11th grade), and on growth trajectories. The two single-time-point analyses will be conducted with Structural Equation Modeling (SEM) using the maximum likelihood method and controlling for baseline levels of substance use and high risk-sexual behavior. The first outcome analysis (posttest) identifies reduction in substance use and high risk-sexual behavior; the second (long-term follow-up) will be used for tests of delayed initiation and reduction of substance use and reduction of high-risk sexual behavior. We will explore, in an additional analysis, SAAF-HS's effects on delaying the onset of sexual intercourse. SAAF-HS, however, is likely to have its strongest impact on growth trajectories (Taylor et al., 2000). A baseline growth model with random intercepts and slopes will be established for the attention-control condition. A multigroup analysis will then be conducted, testing the equivalence of growth parameters between the attention-control and the SAAF-HS groups (Byrne, 2001). If the multigroup analyses detect differences between the slopes (rates of growth for substance use or high-risk sexual behavior) of the SAAF-HS and attention-control group, impact statements will be made by examining how the average substance use and sexual risk behavior trajectories change with time.

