The three-time-point design allows one degree of freedom in fitting linear growth patterns. An exploratory analysis will be conducted to assess nonlinearity in growth over time (Wang, Brown & Bandeen-Roche, 2005). If these diagnostic patterns indicate nonlinearity, the fit will be improved through transformation of the time axis by freeing the last loading, effectively incorporating nonlinearity. Separate analyses will be used to examine impact on alcohol, tobacco, and marijuana use because different intervention impacts occasionally emerge for different substances. In all these models, fit will be compared using formal likelihood ratio statistics, Wald-type tests, and diagnostic techniques that Brown and colleagues developed (Wang, Brown & Bandeen-Roche,

2005). For analyses of high-risk sexual behavior, two outcomes, unprotected sex at last encounter and number of unprotected encounters in the past 3 months, will be analyzed using binary outcomes and Poisson counts, respectively. For each of these repeated measures, we anticipate two types of “zeros”: one indicating abstinence and another indicating condom use. Two approaches will be used, one that incorporates a separate model of abstinence and condom use over time as a function of intervention condition and another that models these outcomes as “zero-inflated” Binomial and Poisson models, similar to Carlin et al.’s (2002) modeling of smoking behavior.

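### SAAF-T's declared primary sexual-risk outcome is undefined for adolescents with no sex in the past 30 days, has no rule for them, and is not named in the analysis plan

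*Combined protocol and SAP*

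**What the plan says.** SAAF-T D.7.7b sets the outcome: "The primary outcome for this variable is the proportion of vaginal and anal sexual acts in which condoms were used during the 30 days" before the computer-assisted interview. It gives the derivation: "This measure is derived by dividing the number of protected encounters by the total number of encounters". It then places two more measures in a secondary list. The first appears as: "Other self-reported sexual behaviors to be assessed include the number of unprotected vaginal and anal sexual encounters during the previous 3 months". The second is whether a condom was used at the latest intercourse.

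SAAF-T D.8.2, headed as the primary-outcome analyses for Aims 1 and 2, has this on sexual risk: "two outcomes, unprotected sex at last encounter and number of unprotected encounters in the past 3 months, will be analyzed using binary outcomes". The count is given a Poisson model. For these two measures the plan expects zeros of two kinds, from abstinence and from condom use. One planned approach "incorporates a separate model of abstinence and condom use over time as a function of intervention condition". A second approach, to be run alongside it, "models these outcomes as “zero-inflated” Binomial and Poisson models". As an additional exploratory analysis D.8.2 will look at the program's "effects on delaying the onset of sexual intercourse".

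The 30-day ratio is not mentioned in D.8. Aim 2 does not mention it either; its examples are instances of unprotected intercourse and having several partners.

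**The concern.** Two things go wrong together. The outcome called primary in the measures section cannot be calculated for adolescents who had no sex in the window, and D.8.1 itself expects many abstainers in the sexual behavior variables. The analysis section then works with other measures. Aim 2 is left with three candidate measures and no statement of which one governs, so the headline result could be chosen after the data are seen.

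If the ratio is used as defined, its denominator depends on sexual activity after randomisation. The program may alter that activity; D.8.2 plans to explore whether it delays onset. The ratio would then compare arms within a subset that treatment may have shaped, which sits badly with the intent-to-treat commitment in D.1.1. A program that works partly by abstinence could look neutral or harmful on it.

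**Working it through.** **1. The two sections side by side**

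| Measure | Status in D.7.7b | Named in D.8.2? | Value for an adolescent with no sex in the window |
|---|---|---|---|
| Condom-use proportion, 30 days | Primary | No | 0/0, no rule |
| Unprotected acts, 3 months | Further behavior | Yes, Poisson count | 0 |
| Condom use at last intercourse | Further behavior | Yes, binary | Abstinence treated as one type of zero |

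The zero-handling in D.8.2 does not carry over to the ratio. For the count, 0 is the best value. For the ratio, 0 would mean that no act was protected, the worst value. Coding abstainers as 0 would reverse their meaning.

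**2. Direction of possible bias (all inputs assumed, for illustration)**

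Before any effect, 20% of an arm are lower-risk active youth (80% of acts protected), 10% are higher-risk active youth (30% protected), and the rest are abstinent. Each active youth has 6 acts. Suppose the program leads a quarter of the lower-risk youth to abstain, so 20% becomes 15%.

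- Mean ratio among the active, before: (.20 × .8 + .10 × .3) / .30 = .19/.30 = .633
- After: (.15 × .8 + .10 × .3) / .25 = .15/.25 = .600
- Unprotected acts per randomised youth, before: 6 × (.20 × .2 + .10 × .7) = .66
- After: 6 × (.15 × .2 + .10 × .7) = .60, a fall of .06/.66 = 9%

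No individual's condom use got worse, and total exposure fell, yet the ratio declined.

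**3. Precision**

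D.8.6 gives an effect size of .25 with 80% power at the .05 level for a continuous outcome at one time point, with 250 per arm and negligible school variation. Sidedness is not stated; I take two-sided.

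Reproduction: power = Φ(.25 × √(250/2) − 1.96) = Φ(.835) = .798. The stated figure holds, provided that all 250 per arm contribute a value.

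The ratio exists only for the share f who were active in the 30 days. The documents do not give f, so I show a range. Detectable effect = (1.96 + .842) × √(2/(250f)):

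| Assumed f | n per arm | Detectable effect, 80% power | Power at .25 |
|---|---|---|---|
| 20% | 50 | .56 | .24 |
| 30% | 75 | .46 | .33 |
| 40% | 100 | .40 | .42 |
| 50% | 125 | .35 | .51 |
| 60% | 150 | .32 | .58 |

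These use the 250 per arm stated in D.8.6. That choice favors the plan, because 500 families less 13% is 435, or about 217 per arm.

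**The case against.** The best defense is that the ratio is not excluded from analysis. D.8.2 says in general terms that the program's impact on every outcome will be examined at posttest, at follow-up and on trajectories. D.8.1 plans two-part models for sexual behavior variables with many abstainers, and D.8.2 adds a separate abstinence and condom-use model. A reader might infer that the ratio will never be analysed; the documents do not support that. They do leave it unnamed, with no model and no denominator rule. The two-part approach does not remove the selection problem, because its condom-use part still conditions on being active after randomisation.

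A reader might also infer that most of the sample drops out. No document gives the 30-day active share, and at 60% most of the sample would stay. Likewise, it is not established that the arms become non-comparable. That requires an effect of the program on recent sexual activity, and the example in the working shows only that bias is possible.

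Third, a reader might infer from the word Poisson that abstainers' zeros are ignored and that false positives are inflated by a calculable amount. Zeros are addressed explicitly. D.8.1 and D.8.2 also provide for exploratory choice of model, random intercepts and slopes, and fit diagnostics, any of which could absorb or reveal extra variation. No dispersion value is given, so no false-positive rate can be attached to the plan. What stands is narrower: SAAF-T names no negative binomial model, robust standard errors or other provision for overdispersion among the positive counts. AIM's plan does name the negative binomial, but that is a different trial.

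**Conclusion.** The core holds on the text alone. The declared primary for high-risk sexual behavior has no value for adolescents without recent sex, no rule for them and no named analysis, while D.8.2 analyses two measures ranked below it. D.7.7b and D.8.2 must be reconciled before Aim 2 has an interpretable primary test.

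The size of the problem depends on assumptions. The fall from .63 to .60 alongside a 9% reduction in unprotected acts rests on invented rates and shows direction only. The detectable effect of about .56–.32 rests on an assumed 20–60% active. The comparator of .25 is a general figure for continuous outcomes; D.8.6 gives none for the ratio. What does not depend on the assumed share is that 250 values per arm are needed to reach .25, so the ratio falls short unless nearly everyone is active. The overdispersion gap is secondary and unquantified.

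**What to change.** In D.7.7b, name as the Aim 2 primary the number of unprotected vaginal and anal acts in the past 3 months, with abstinent youth counted as 0, in all randomised adolescents. This measure is already collected, is already in D.8.2, fits Aim 2's own example, and is defined for every assessed adolescent.

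In D.8.2, make the primary contrast the overall mean count between arms, adjusted for pretest, by negative-binomial regression or by Poisson regression with robust standard errors. The overall mean matters: the positive-count part of a hurdle or two-part model again conditions on behavior after randomisation. Keep the two-part and zero-inflated models as supporting analyses. Report the 30-day ratio as secondary, among the sexually active, labelled as a non-randomised description.

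No new data are needed, but changing a primary outcome is a design decision as well as a wording change. The recall window lengthens from 30 days to 3 months, and D.7.7b values short recall. D.8.6 has no figure for a count outcome, so a power calculation with a stated mean and dispersion must be added. Keeping the ratio as primary with a defined population and a paired abstinence model would close the gap in wording, but the ratio itself would still not be a comparison of the groups as randomised.
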